## Abstract

**Background:**

There is strong evidence of an association between chronic kidney disease (CKD) and cardiovascular disease. To date, however, proof that a reduction in glomerular filtration rate (GFR) is a causative factor in cardiovascular disease is lacking. Kidney donors comprise a highly screened population without risk factors such as diabetes and inflammation, which invariably confound the association between CKD and cardiovascular disease. There is strong evidence that increased arterial stiffness and left ventricular hypertrophy and fibrosis, rather than atherosclerotic disease, mediate the adverse cardiovascular effects of CKD. The expanding practice of live kidney donation provides a unique opportunity to study the cardiovascular effects of an isolated reduction in GFR in a prospective fashion. At the same time, the proposed study will address ongoing safety concerns that persist because most longitudinal outcome studies have been undertaken at single centers and compared donor cohorts with an inappropriately selected control group.

**Hypotheses:**

The reduction in GFR accompanying uninephrectomy causes (1) a pressure-independent increase in aortic stiffness (aortic pulse wave velocity) and (2) an increase in peripheral and central blood pressure.

**Methods:**

This is a prospective, multicenter, longitudinal, parallel group study of 440 living kidney donors and 440 healthy controls. All controls will be eligible for living kidney donation using current UK transplant criteria. Investigations will be performed at baseline and repeated at 12 months in the first instance. These include measurement of arterial stiffness using applanation tonometry to determine pulse wave velocity and pulse wave analysis, office blood pressure, 24-hour ambulatory blood pressure monitoring, and a series of biomarkers for cardiovascular and bone mineral disease.

**Conclusions:**

These data will prove valuable by characterizing the direction of causality between cardiovascular and renal disease. This should help inform whether targeting reduced GFR alongside more traditional cardiovascular risk factors is warranted. In addition, this study will contribute important safety data on living kidney donors by providing a longitudinal assessment of well-validated surrogate markers of cardiovascular disease, namely, blood pressure and arterial stiffness. If any adverse effects are detected, these may be potentially reversed with the early introduction of targeted therapy. This should ensure that kidney donors do not come to long-term harm and thereby preserve the ongoing expansion of the living donor transplant program (NCT01769924).

## Background and rationale

The robust epidemiologic evidence that shows chronic kidney disease (CKD), as manifest by reduced estimated glomerular filtration rate (eGFR), is associated with increased cardiovascular morbidity and mortality provides a strong rationale for a prospective study to determine the cardiovascular effects of kidney donation. A graded inverse relationship exists between cardiovascular risk and eGFR^1^; deleterious cardiovascular effects are clearly evident once eGFR falls to <60 mL/min per 1.73 m^2^, although the exact threshold at which cardiovascular risk becomes elevated remains contentious.^2^, ^3^ Although most data indicate that the cutoff lies between 60 and 70 mL/min per 1.73 m^2^, it may be even higher; in a meta-analysis of general population cohorts with a median follow-up of about 8 years and more than 5 million person-years, mortality rose exponentially once eGFR fell below 75 mL/min per 1.73 m^2^.

Every year, more than 6,000 US individuals undergo elective nephrectomy for the purposes of live donation without apparent increased long-term mortality or cardiovascular risk.^4^, ^5^ Uninephrectomy may be qualified as an “acute kidney injury,” with an immediate 50% reduction in GFR followed by an improvement related to hypertrophy in the remaining kidney—but only to 60% to 70% of baseline.^6^ Up to two-thirds of donors after nephrectomy fulfil the criteria for CKD stage 3 (eGFR, 30-59 mL/min per 1.73 m^2^) dependent on baseline age and renal function,^7^ which has an approximate odds ratio for cardiovascular disease of between 2 and 4 in the general population.^8^ To date, however, all studies examining the long-term consequences of kidney donation have been reassuring, often showing better health outcomes in donors compared with the general population.^4^, ^9^, ^10^ Small adverse cardiovascular effects of donation cannot be excluded, however, because of residual confounding from selection and follow-up biases. Most donors are highly motivated individuals, often making healthy lifestyle choices both before and after nephrectomy. This inherent altruistic nature, in conjunction with the rigorous medical selection procedures for donors, results in an extreme low-risk population, for whom it is near impossible to identify a control cohort of equivalent health status from the general population. This makes well-controlled studies difficult, and thus, far we are aware of only one published prospective, controlled pathophysiologic study of kidney donors.^11^

The mechanisms by which CKD exerts adverse effects on cardiovascular structure and function are diverse and have been the subject of recent reviews.^12^, ^13^ Leading potential mediators include increased arterial stiffness, hypertension, increased left ventricular (LV) mass and abnormal bone mineral metabolism, which may lead to increased vascular calcification.^12^ There is strong cross-sectional evidence that aortic pulse wave velocity (aPWV; a validated measure of arterial stiffness) increases as GFR falls.^14^, ^15^, ^16^ In a community-based study, among treated hypertensive patients, even minimally impaired baseline renal function was associated with an increased rate of aortic stiffening.^17^ Aortic PWV is an independent predictor of all-cause and cardiovascular mortality in many populations including patients on dialysis,^18^, ^19^ and failure to lower aPWV by angiotensin-converting enzyme inhibitors and blood pressure reduction has been associated with reduced survival.^20^ To date, only one study examining arterial stiffness in kidney donors after nephrectomy has been published.^21^ This had a cross-sectional observational design, comparing 101 kidney donors at a mean of 111 ± 42 months from donation with healthy controls matched only for age and gender, indicating that aPWV was significantly higher in donors. In a recent uncontrolled study of 17 donors, although aPWV was not examined, augmentation index and central arterial pressure were unchanged at 6 months compared with baseline.^22^

With respect to the effects of kidney donation on peripheral blood pressure, the data are inconclusive, but the best available evidence from a meta-analysis suggests a moderate increase of about 5 mm Hg in systolic pressure at 10 years after donation.^23^ Although high-quality prospective studies of donors are still required, in the general population, even a 2-mm Hg increase in systolic blood pressure is associated with a long-term increase in mortality of about 10% for stroke and 7% for ischemic heart disease.^24^ Thus, it appears that either the adverse effects of hypertension in kidney donors are small and as yet undetected by clinical end point studies or that regular medical supervision postdonation has allowed early initiation of antihypertensive therapy and thereby prevented harmful sequelae.

Increased LV mass is an almost universal finding by late-stage CKD^25^ and is recognized as an important mediator of morbidity and mortality due to heart failure and lethal arrhythmia, the commonest modes of death in CKD.^26^ Chronic Kidney Disease–Mineral and Bone Disorder (CKD-MBD) is driven by impaired phosphate excretion resulting in both bone disease and vascular calcification, which, in turn, mediates increased arterial stiffness and adverse LV remodeling.^27^, ^28^ Markers of CKD-MBD such as phosphate, fibroblast growth factor 23 (FGF-23), and parathyroid hormone (PTH) predict mortality and adverse cardiovascular events in patients with CKD.^29^ Furthermore, there is evidence from community-based studies of graded associations between phosphate and LV mass, cardiovascular events, and death.^30^ Further detailed information is therefore required on the effect of kidney donation on both LV mass and markers of CKD-MBD. A 23% increase in PTH has already been reported in kidney donors at 6 months after nephrectomy compared with controls.^11^

Although reduced eGFR is strongly associated with increased cardiovascular risk, this relationship may not be causal: CKD has a powerful clustering effect for other cardiovascular risk factors such as hypertension, diabetes, dyslipidemia, and inflammation, which may confound the association. Kidney donors provide an ideal “human model” that enables the longitudinal study of the cardiovascular effects of a reduction in GFR in isolation without the multiple confounding factors associated with renal disease. The proposed study will prospectively examine the effects of unilateral nephrectomy on the potential pathophysiologic mechanisms that appear to mediate cardiovascular morbidity and mortality in CKD, namely, arterial stiffness and blood pressure as primary end points, and LV mass and CKD-MBD parameters as nested substudies, in a cohort of kidney donors large enough to allow the detection of small effect sizes.

### Hypotheses

In living kidney donors, the reduction in GFR that accompanies nephrectomy results in (1) a pressure-independent increase in aortic stiffness (aPWV), (2) an increase in blood pressure, (3) an increase in LV mass and impairment in LV diastolic function, and (4) adverse effects on bone mineral metabolism.

## Methods

### Study design

This is a prospective, multicenter, longitudinal, parallel group study of 440 living kidney donors and 440 healthy controls to be recruited for 2 years with initial follow-up of 12 months. All participants will undergo informed written consent in keeping with the principles set out by the Declaration of Helsinki. The EARNEST study received research ethics approval in February 2013. The study is funded by the British Heart Foundation and registered with the US National Institutes of Health database (NCT01769924).

### Study population

The inclusion and exclusion criteria for both donor subjects and controls are outlined in Table I and are identical to those set by the UK living kidney donor guidelines compiled by the Joint Working Party of The British Transplantation Society and The Renal Association.^31^ The only inclusion criterion is that donor subjects will be scheduled for nephrectomy for the purpose of kidney donation. A carefully matched series of control patients will be recruited from the same living donor clinics at which subjects are identified, who, after screening, are found to be fit for donation but do not proceed to surgery (eg, because of arterial anatomy and immunologic mismatch). If appropriate, donor-related family members will also be invited to participate in the study as healthy controls to provide a closely matched control population with equivalent baseline health status to the donor cohort.

**Table I t0005:** Inclusion and exclusion criteria

Inclusion criteria
Age 18-80 y
Acceptable GFR by donor age before donation⁎
Exclusion criteria
Hypertensive end-organ damage, uncontrolled hypertension or the requirement for >2 antihypertensive medications
Significant proteinuria†
LV dysfunction
Diabetes mellitus
Atrial fibrillation
Any history of cardiovascular or pulmonary disease that would preclude kidney donation

⁎ Based on the anticipation of having an eGFR of >50 mL/min per 1.73 m^2^ aged 70 years.

† ACR >30 mg/mmol, PCR >50 mg/mmol, or 24-hour total protein >300 mg/d.

Participants will be recruited from the following core centers, chosen because of their high numbers of live donor transplants and strength in vascular research: (1) Queen Elizabeth Hospital Birmingham, England; (2) Addenbrooke's Hospital, Cambridge, England; (3) Western Infirmary Glasgow, England; (4) University Hospital Coventry and Warwick, England; (5) Southmead Hospital, Bristol, England; (6) Northern General Hospital, Sheffield, England; and (7) Belfast City Hospital, Belfast, North Ireland. This study remains open to the inclusion of additional transplant centers from inside and outside the UK.

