#### Blood and urine

Routine hematologic and biochemical parameters will be recorded, including hemoglobin, creatinine, calcium, albumin, glucose, phosphate, and PTH. A series of biomarkers will also be measured including N-terminal prohormone of brain natriuretic peptide, uric acid, urinary albumin/creatinine ratio (ACR), and fractional excretion of sodium.^43^, ^44^, ^45^

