### Statistical analysis

The formal comparison between arms of each of the coprimary end points will use a linear regression model on the within-patient change from baseline, adjusting for baseline value, sex, ethnicity, use of antihypertensives, age, eGFR at donation (and iGFR where available in donors), and the other coprimary end point at baseline. To formally control the overall significance level over both coprimary end points (aPWV and blood pressure) at 5%, a Holm-Bonferroni method will be used. Findings will be interpreted taking into consideration that aPWV and blood pressure are correlated. A secondary analysis of the coprimary end points will be performed according to age, ethnic group, baseline eGFR and change in eGFR (and isotopic GFR where available in donors), BMI, and predonation hypertension.

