## Discussion

There is strong evidence that patients with CKD have increased cardiovascular risk with a graded relation with both eGFR and the level of albuminuria.^62^ However, previous studies are limited by their cross-sectional and observational nature, and causation has not yet been established. The true impact of CKD on the cardiovascular system remains hard to define because the duration of the CKD is often unknown, the underlying causes are diverse, and there are numerous confounders including associated diseases such as hypertension and diabetes. Moreover, the level of GFR at which adverse structural and functional changes occur within the heart and vasculature and at which cardiovascular risk starts to rise is not clear. Kidney donors provide a unique healthy population who change at a known time point from having normal to impaired renal function. This study should establish whether reduced GFR leads directly to adverse cardiovascular effects such as increased arterial stiffness, hypertension, LV mass, and mineral bone disorder. Because the prevalence of CKD is high and rising (14.0% in the United States in 2005-2010, as defined by eGFR <60 mL/min per 1.72 m^2^ or ACR ≥30 mg/g),^26^ it is important to establish if a causal relationship exists to determine whether targeting CKD alongside more traditional risk factors could lead to reductions in cardiovascular mortality and morbidity. The potential size of this effect is salutary. If causative, it has been estimated that up to 10% of vascular events in middle age and 20% in old age might be attributable to reduced eGFR.^63^

By careful prospective measurement of ambulatory blood pressure in living kidney donors before and after nephrectomy, this study will also provide important practical information needed for patient care. By clarifying whether there is an increased frequency of hypertension and surrogate markers of cardiovascular disease after donation, we will be able to better advise potential donors in future and inform national guidance on the importance of long-term follow-up.

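### Participants with albuminuria between about 3.4 and 30 mg/mmol can enter either arm, and the stated coprimary model adjusts for eGFR but not for baseline ACR, which is already collected

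*Protocol article*

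**What the plan says.** **Entry.** Under Study population, the article states that "The inclusion and exclusion criteria for both donor subjects and controls are outlined in Table I". The Table I footnote defines significant proteinuria as "ACR >30 mg/mmol, PCR >50 mg/mmol, or 24-hour total protein >300 mg/d". The GFR criterion is "Based on the anticipation of having an eGFR of >50 mL/min per 1.73 m^2^ aged 70 years", and no floor of 60 is stated. The section says that the criteria are those of the UK living donor guideline.

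**Baseline renal status.** The Discussion describes the donors in these words: "Kidney donors provide a unique healthy population who change at a known time point from having normal to impaired renal function". It opens by saying that cardiovascular risk in CKD is graded with eGFR and also with albuminuria. Further on it quotes a US prevalence of CKD, "as defined by eGFR <60 mL/min per 1.72 m^2^ or ACR ≥30 mg/g".

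**Data.** The Blood and urine section lists "uric acid, urinary albumin/creatinine ratio (ACR), and fractional excretion of sodium" among the measurements, and Table II lists ACR as a secondary outcome. Investigations are made in all participants at baseline and 12 months.

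**Analysis.** Under Statistical analysis, the coprimary comparison is a linear regression on within-patient change, "adjusting for baseline value, sex, ethnicity, use of antihypertensives, age, eGFR at donation", with isotopic GFR where available in donors and the other coprimary endpoint at baseline. The factors for the secondary analysis of the coprimary endpoints are age, ethnic group, baseline eGFR and its change, BMI and predonation hypertension. ACR is in neither list.

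**The concern.** The study's case for causality is that donors lose GFR and nothing else, starting from healthy kidneys. The document itself treats albuminuria as a second axis of renal cardiovascular risk, separate from eGFR. The entry rule leaves a wide range of that axis open, and the model adjusts for only one of the two axes.

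This would matter little in a randomised trial. Here the controls are people who were fit to donate but did not proceed, together with donors' relatives, so equal ACR distributions in the two arms cannot be taken for granted. Adjusting for baseline aPWV and blood pressure deals with differences in starting level. It does not deal with a factor that changes the rate of progression over the year. The Background gives some reason to think that such a factor may exist: it cites faster aortic stiffening with even slightly impaired renal function in treated hypertensive patients, and Table I admits people on up to two antihypertensive drugs.

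At stake is how firmly a donor-control difference can be attributed to the fall in GFR alone.

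**Working it through.** The plan gives no figure of its own for the albuminuria band, so there is none to reproduce. The steps are a unit conversion, a check on the other two limits, and a bound on the possible bias.

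**1. Conversion.** Assumption from outside the documents: the molar mass of creatinine is 113.12 g/mol (a physical constant), so 1 mmol = 0.11312 g.

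- Table I limit: 30 mg/mmol / 0.11312 g/mmol = 265.2 mg/g.
- Limit in the cited CKD definition: 30 mg/g × 0.11312 g/mmol = 3.39 mg/mmol.
- Ratio: 265.2 / 30 = 8.84.

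On the ACR limit alone, the open band is about 3.4 to 30 mg/mmol.

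**2. Do the other two limits close the band?** The three are joined by *or*.

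- PCR 50 mg/mmol is 50 / 0.11312 = 442 mg/g of total protein.
- For 300 mg/d of protein, ACR = (300 / daily creatinine) × albumin share. Assumed ranges: creatinine 6 to 16 mmol/d, albumin 30% to 70% of urine protein.
  - Lowest: 300 / 16 × 0.3 = 5.6 mg/mmol (50 mg/g, 1.7 times 30 mg/g).
  - Highest: 300 / 6 × 0.7 = 35 mg/mmol (309 mg/g), where the ACR limit of 30 would act first.
  - At 10 mmol/d: 300 / 10 × 0.3 to 0.7 = 9 to 21 mg/mmol.

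Where a 24-hour collection is made, the effective ceiling may be well below 30 mg/mmol, but over the whole assumed range it stays above 3.4. ACR is the only urine protein test listed among the study's own measurements.

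**3. How many people?** Not given. As an assumed range, 1% to 5% of 880 is 8.8 to 44 people.

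**4. Bound on the bias.** Bias in the mean difference ≈ (difference between arms in the share of people in the band) × (extra one-year change in those people). The most unfavourable split of the upper assumption puts all 44 in one arm of 440, a difference in share of 44 / 440 = 10%.

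| Assumed extra change | Bias | Target difference |
|---|---|---|
| aPWV 0.2 m/s | 0.10 × 0.2 = 0.02 m/s | 0.22 m/s |
| aPWV 1.0 m/s (one SD) | 0.10 × 1.0 = 0.10 m/s | 0.22 m/s |
| Blood pressure 10 mm Hg (one SD) | 0.10 × 10 = 1.0 mm Hg | 2.2 mm Hg |

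With 9 people in one arm (9 / 440 = 2%), the one-SD row for aPWV falls to 0.02 m/s. The SDs and target differences are those in the sample size section.

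**5. Sample size.** It is not affected. At a 2.5% two-sided level and 80% power, a difference of 0.22 m/s with SD 1.0 needs 393 per group, against the stated 400, and 400 / 0.91 gives the 440 recruited.

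**The case against.** The strongest reply has four parts.

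**The limits do not conflict.** A reader might infer that Table I contradicts the document's own definition of CKD. The documents do not support that. The ACR limit of 30 mg/g only explains how a cited US prevalence figure was defined and governs no eligibility rule, outcome or analysis. The entry limit is a declared adoption of the donor guideline. The sentence on normal and impaired function follows one about the level of GFR and can be read as being about filtration. This part stands in full.

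**Nobody is shown to be in the band.** A reader might also infer that people with CKD do enter. The rule permits ACR values in that range, but the article gives no count, and everyone must be fit for donation. This stands too: the point is about who can enter.

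**The design already limits bias.** The outcome is within-patient change, both arms have the same criteria, and the model adjusts for baseline aPWV and blood pressure, eGFR, age and antihypertensives. This stands in large part. What remains is a different one-year course combined with imbalance between the arms.

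**This belongs in the SAP.** A restricted-set analysis may well be in a plan that is not shown, so its absence here is no fault. The covariates are different: the article states them as an explicit list, and ACR is not on it.

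One further inference should be set aside, namely that rises in ACR as a secondary outcome are pooled whatever their starting value. The article does not say how secondary ACR is analysed.

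**Conclusion.** The point holds as a modest, inexpensive improvement to the analysis. It is not an error in the entry rule. Participants with ACR from about 3.4 up to at most 30 mg/mmol can enter either arm. The document regards albuminuria as a graded risk marker, the comparison is not randomised, and the stated model covers eGFR but leaves out an ACR value that is already measured.

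The likely size is small. Under the assumption of 1% to 5% in the band, even the most lopsided split with a full SD of extra change gives 0.10 m/s, a little under half of the 0.22 m/s target (0.10 / 0.22 = 45%). More moderate assumptions give 0.02 m/s or less. The prevalence, the split and the extra change are all assumed, so these figures bound the effect and do not estimate it. Bias is possible and has not been shown. What is exposed is the claim that a fall in GFR alone, from normal renal function, drives any effect.

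**What to change.** - Leave enrolment unchanged.
- Add log baseline ACR to both coprimary regression models, with a rule fixed in advance for values below the assay's reporting limit.
- Add one sensitivity analysis of both coprimary endpoints in participants with baseline ACR below 3.4 mg/mmol (30 mg/g) and eGFR of at least 60 mL/min per 1.73 m². Report it as support for the claim about a fall in GFR from normal renal function: agreement with the main result strengthens that claim, and disagreement would call for more cautious wording.
- As a clerical matter, give both ACR limits in the same unit where they appear.

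If an SAP already contains the restricted analysis, only the covariate needs attention. The cost is one more regression term, from data already planned for every participant, and a slightly smaller set in the sensitivity analysis. Sample size, visits and measurements do not change.
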